## Abstract

**Background:**

Obstructive sleep apnea (OSA) is a sleep disorder that disproportionately affects African Americans (hereafter referred to as blacks). Moreover, blacks may underutilize sleep services including overnight polysomnography. Thus, OSA among blacks may go undiagnosed and untreated, which has significant health consequences, including hypertension, diabetes, cognitive impairment, and daytime sleepiness.

**Design and Methods:**

This two-arm randomized controlled trial will assign 200 participants to a culturally and linguistically tailored web-based sleep educational platform. The website will be developed to ensure that the content is user friendly and that it is readable and acceptable by the target community. Participants will receive login information to a password-protected website and will have access to the website for 2 months. Study assessments will be collected at baseline, 2 months (post-enrollment) and at 6 months (follow-up). We will use qualitative and quantitative methods to develop tailored materials and to ascertain whether tailored materials will increase OSA knowledge and OSA health literacy by comparing blacks exposed to tailored materials versus those exposed to standard sleep health literature. We hypothesize that exposure to tailored OSA information will improve OSA health literacy.

**Discussion:**

Few studies have investigated the racial/ethnic disparities in relation to OSA screening and treatment comparing blacks and whites. Moreover, we know of no interventions designed to increase OSA knowledge and health literacy among blacks. Use of the Internet to disseminate health information is growing in this population. Thus, the Internet may be an effective means to increase OSA health literacy, thereby potentially increasing utilization of sleep-related services in this population.

**Trial registration:**

The study is registered at clinicaltrials.gov, reference number NCT02507089. Registered on 21 July 2015.

## Background

Increasingly, researchers and practitioners recognize that obstructive sleep apnea (OSA) - one of the most commonly diagnosed sleep disorders - disproportionately affects blacks. One of the earliest studies documenting racial/ethnic differences in the rate of OSA compared 225 black and 622 white volunteers, ages 2–86 years, and found that 31% of blacks versus 10% of whites had OSA [1]. More recent studies have also reported similar disparities including adherence to OSA treatment, with blacks using positive airway pressure (PAP) far less than their white counterparts [2–4]. The underlying mechanisms of these disparities are not clear. However, research suggests that the disparities in OSA prevalence may be explained by genetic factors and obesity [5], while disparities in treatment adherence may be partially explained by socioeconomic status [3] and sleep duration [2].

The Institute of Medicine and the National Institutes of Health (NIH) recognize OSA as a chronic disease that requires novel adherence strategies to promote enhanced quality of life and diminish social and economic costs [6]. Yet, our pilot data suggests that blacks tend to underutilize sleep services. This is unfortunate given that there may be a high prevalence of OSA in this community, and that treatment is effective in improving cardiovascular disease (CVD) risk factors, especially blood pressure [7], which disproportionately burden blacks.

### Insufficient sleep and sleep disorders

A recent analysis of data from 12 states conducted by the Centers for Disease Control and Prevention (CDC) illustrated that 35.3% of United States (US) adults reported insufficient sleep and 37.9% reported unintentionally falling asleep during the day [8]. It also appears that there is increased awareness about sleep in the general population. For example, using the National Ambulatory Medical Care Survey, Ford et al. [9] found a 13% increase in the number of physician office visits for sleep complaints and a 200% increase in the number of individuals who reported a sleep disorder diagnosis including OSA, insomnia, and restless leg syndrome. As there appears to be an increase in sleep complaints and diagnoses of sleep disorders, as well as the rapidly growing field of sleep medicine, it is paramount that patients be educated about sleep health, including the importance of screening and adhering to treatment, especially among minority populations who may underutilize sleep services. Blacks as well as other racial/ethnic groups with untreated OSA may be at greater risk for hypertension [10], diabetes [7], cognitive impairment [11], and poor quality of life [12].

### Sleep and health literacy

Health literacy is defined as “the degree to which individuals can obtain, process, and understand basic health information, and services they need to make appropriate health decisions” [13]. Health literacy requires several skills including print literacy (reading and writing), numeracy (recognizing numbers in the case of a prescription), and oral literacy (listening and speaking). It is estimated that 77 million Americans have limited health literacy, costing the healthcare system $106–238 billion a year [14].

Limited health literacy is a major problem in the US, and health literacy is linked to delayed diagnoses, lack of understanding of medical condition, lack of treatment, poor self-management skills, and worse clinical outcomes [15]. Greater rates of limited health literacy are generally reported among minorities, the elderly, and individuals with low educational attainment. A systematic review indicated that patients with low health literacy were generally 1.5 to 3 times more likely to experience poor health outcomes [16].

Patients with limited health literacy may experience difficulty locating providers and services, completing complex health forms, sharing their medical history with providers; they may also be unaware of the link between health risk behavior and poor health outcomes. It is plausible, then, that describing symptoms of sleep disturbance, undergoing screening for sleep disorders, and adhering to treatment, particularly PAP, would require high-level literacy skills. In a cohort of men from Australia who underwent polysomnography, low functional health literacy, another measure of health literacy, was one of the main factors associated with previously undiagnosed OSA (OR = 2.43, 95% CI = 1.40–4.20) compared to men with adequate functional health literacy [17]. These findings also suggest that health literacy is associated with the uptake of OSA screening.

The Centers for Medicare and Medicaid Services requires that the patient use PAP for 4 or more hours per night, 70% of nights in a 30-day period for reimbursement [18]. In addition to the lack of empirical evidence to support this guideline as a necessary and sufficient marker of adherence, this information might be difficult for patients to comprehend; patients may be unable to process the amount of time that they are required to use their PAP mask accurately in order to achieve adherence. In addition, adherence to PAP may require a high level of oral communication skills whereby patients should be able to communicate with their provider whether or not they are experiencing challenges with mask use; the PAP mask may involve several challenges including negative side effects and mask discomfort [19]. It is plausible that some of the adherence issues may be exacerbated when coupled with mental health problems, and there is a high rate of depression among patients diagnosed with OSA. In effect, in an analysis of the 2005–2008 National Health and Nutrition and Examination Survey, Wheaton et al. [20] reported that the rate of depression was two and five times more likely to be reported among men and women, respectively, who were diagnosed with OSA. Thus, adhering to physician recommendations for OSA screening and treatment requires a high degree of health literacy, and there may be significant consequences for those patients with low literacy skills.

Similarly, patients may have difficulty completing commonly used sleep surveys. One study found that 56% of new sleep patients had difficulty completing the Epworth Sleepiness Scale, a commonly used measure for describing sleep symptoms [21]. In another study, 44% of patients with low literacy skills required assistance reading National Sleep Foundation (NSF) and American Academy of Sleep Medicine (AASM) brochures [22]. Using the Rapid Estimate of Adult Literacy in Medicine [23] questionnaire, a survey of patients from 122 sleep centers showed that 16.3% exhibited impaired health literacy [21]. Of note, the Center for Health Care Strategies does not recommend such tools in communities characterized by low literacy levels and trust [24–27], unless these materials are specifically tailored for the intended community [28].

### Objectives

Despite these limited studies, which have significant implications for the field of sleep medicine, we know of no interventions to improve adherence to treatment for sleep disorders or adherence to physician recommendations for sleep screening among patients with low health literacy. Our primary objective is to develop the Tailored Approach to Sleep Health Education (TASHE) program using a multilevel community-engaged approach. We will use themes ﻿from focus group to develop a culturally and linguistically tailored wbsite and video vignettes. We will incorporate those themes into an interactive website with OSA health content designed for lay people. This website will thus serve as a platform facilitating exchange of information between sleep scientists, community health providers, potential patients, and lay health advisors. We will also seek endorsement of TASHE materials by healthcare providers and stakeholders to ensure their adoption and dissemination. Our secondary objective is to evaluate TASHE’s effectiveness in increasing OSA health literacy among blacks. The main hypotheses for this study are: (1) modifiable barriers (e.g., negative beliefs and attitudes toward sleep, perceived bias in healthcare, inadequate access, and lack of cultural and linguistic tailoring of sleep health materials to blacks) will comprise emergent themes from focus groups; (2) participant engagement will increase acceptability of sleep health messages. Stakeholder engagement will facilitate adoption, dissemination, and sustainability of the program. Provider engagement will enable tailoring of messages addressing patient’s concerns about effectiveness, benefits, and harms of treatment options to inform decision-making; and (3) exposure to tailored OSA health messages will improve OSA health literacy.

## Design and methods

This two-arm randomized controlled trial will include use of an interactive, culturally and linguistically tailored website for blacks at risk of OSA. The secondary objective is to increase knowledge about OSA and improve OSA health literacy. The approach was designed based on the formative evaluation that was conducted in the NIH-funded study ‘Metabolic Syndrome Outcome Cohort’ study [29, 30] in which results from focus groups included misperceptions about OSA and mistrust of the healthcare system [31, 32]. Results of that study suggested the need to use an innovative approach to increase OSA knowledge and OSA health literacy via a web-based platform.

## Study design and overview

### A community-engaged approach

We will bring together academic investigators, community providers, and stakeholders, which is considered to be an effective tool to develop interventions, sustainable programs, and policies to address health disparities, and to improve adoption of healthful practices in underserved communities [33, 34]. This partnership approach begins with a research topic of importance to the community (i.e., sleep apnea) and combines knowledge with action to achieve social change in order to improve health outcomes and eliminate health disparities [35]. It is becoming increasingly evident that community engagement in the research process is critical. Doing so leads to identification or refinement of relevant research questions [36], delineates barriers, increases community participation in research [37], improves effectiveness of interventions [38], and enhances dissemination of study results [36] (see Fig. 1).

**Fig. 1 Fig1:**
[figure not shown]
Multi-level Community-engaged approach

### Faculty advisory board

We will convene a Faculty Advisory Board (FAB) comprised of the leading sleep medicine physicians, scientists, and researchers, which will be tasked to help develop (review and approval) the sleep health content of all TASHE materials before dissemination. This will ensure that materials emphasize current concepts and understanding regarding sleep health and circadian and sleep biology and promulgate important findings of the National Heart, Lung, and Blood Institute (NHLBI)-funded clinical trials.

### Community steering committee

Our experience conducting minority research has informed us that interventions are best poised to be effective and sustainable when they are culturally appropriate and responsive, and that stakeholders in the partner community endorse them, such that the end result is increased empowerment of community members to address their own health issues. Community academic partnerships, as we have assembled to achieve goals of the TASHE project, have significant advantages over efforts undertaken by researchers alone because such partnerships bring a diversity of expertise that facilitates a more comprehensive understanding of community strengths and needs, as well as improved capacity to plan, execute and evaluate the project. We will create a Community Steering Committee (CSC) [39] bringing together community stakeholders, patients, and health advocates to work with the TASHE project leadership and the FAB. In addition, the CSC will provide feedback on the content of the website to ensure that it reflects the voice of the community and to provide feedback on other programmatic areas including design features and content of the website. The CSC will receive a summary of all research-related findings including themes from the focus groups and preliminary study results throughout the study period.

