### Website development

The content of the website will be based on several resources: (1) the FAB and members of the investigative team will advise on the content that should be included and develop all necessary informational sections; (2) a literature review; and (3) a review of existing sleep-related websites and brochures including the AASM, the NHLBI, and the NSF. The FAB will review the content for accuracy and completeness. The content will then be presented to the CSC, which will provide additional suggestions and comments; these will be incorporated into the final content used in the website. The investigative team will review the content to assess health literacy including ease of use, design layout, and readability. We will use the Flesch-Kincaid readability formula and the material will be customized at the fifth-sixth grade reading level.

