### Recruitment

We will use several recruitment strategies. First, we will utilize a recruitment funnel that we have developed from several other Institutional Review Board (IRB)-approved NIH-funded studies related to sleep health. Participants will be contacted via phone to ascertain their level of interest. If participants express interest, they will be invited to come to our office at New York University. Then, a member of the research team will provide detailed information about the study protocol, and read the consent form. Participants will have time to ask questions.

Second, we will host information sessions with prospective participants. These sessions will last approximately 20 minutes and will be led by a senior member of the investigative team. The purpose of the session is to (1) provide detailed information about the study protocol, (2) discuss requirements and expectations of participants, and (3) ascertain interest in moving forward with the study. Participants will receive information materials and a consent form that they may take home to discuss with their family, friends, or doctor, before they agree to sign the consent form. This will allow participants enough time to make an informed decision about whether or not to participate in the study. Participants will have time to answer questions of the investigative team.

Third, we will rely on established relationships with community-based and faith-based organizations including barbershops and churches. Through these efforts, the research team is able to go on site to gauge participant interests. We will follow the same procedures throughout the study, which involve: (1) providing detailed information about the study, (2) providing study materials for participants to review on their own time, and (3) allowing participants enough time to ask questions freely.

Finally, recruitment materials including flyers, brochures, and fact sheets will be developed in conjunction with the CSC. These materials will be at the fifth-sixth grade reading level. All materials provide an overview of what is involved in participating in the study, and will be placed in community venues including barbershops, community-based organizations, and churches. The CSC members will provide feedback to ensure that the materials are clearly written, and that they are acceptable to the community. The Project Manager in consultation with the Principal Investigator (PI) will oversee recruitment and consent.

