### Allocation

Individuals will be eligible for randomization once their baseline questionnaire is completed. Randomization will be carried out in pairs using a table of random permutations conducted by the Program Manager. One member of each pair will be assigned to the Internet-based group and the other to the control group, using sealed envelopes. This strategy ensures equal allocation to the two groups, and that both have similar characteristics regarding measured and unmeasured background variables (i.e., patient characteristics and lifestyle behavior at baseline, medical comorbidities, and situational/contextual factors), which could potentially affect study outcomes. The Program Manager will hold the sequence of assignments and will dispense the code for each new patient upon request by the Research Assistant (RA). If a participant requests to be withdrawn from the study, the Program Manager will assign the code for the next new patient. The Program Manager  will maintain a record of who was randomized to which group to maintain integrity of planned analysis. Due to the nature of the study, the Program Manager will not be blind to the study arms. Randomization will be ongoing until sample size goals are reached: 100 per study arm and in accordance with the CONSORT randomization guidelines as shown in Fig. 2.

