## Data monitoring

In compliance with NIH requirements, we will establish a data safety and monitoring plan (DSMP). The purpose of the DSMP is to ensure the safety of participants and the validity and integrity of the data. In adherence to NIH policy regarding data sharing, the DSMP will be tasked to develop its data-sharing plan in consultation with an external representative. Data will be made available from the institutions’ website once the main findings of the project have been published. The plan will incorporate language to ensure that the rights and privacy of people who participate in NIH-sponsored research are protected at all times. Thus, data will be free of identifiers that would permit linkages to individual research participants and variables that could lead to deductive disclosure of individual participants. The DSMP internal committee will review all requests for data before access to the data is granted.

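### The Community Steering Committee is promised preliminary study results throughout the study, and the article does not exclude outcome results by arm

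*Protocol article*

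**What the plan says.** Under Community steering committee, the protocol article describes a committee "bringing together community stakeholders, patients, and health advocates to work with the TASHE project leadership and the FAB". On what the committee is told, it says: "The CSC will receive a summary of all research-related findings including themes from the focus groups and preliminary study results throughout the study period".

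The committee's other tasks appear elsewhere. Under Recruitment, "recruitment materials including flyers, brochures, and fact sheets will be developed in conjunction with the CSC", and these materials are placed in community venues. Under Website development, "The content will then be presented to the CSC, which will provide additional suggestions and comments".

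Under Allocation, "Randomization will be ongoing until sample size goals are reached", the goal being 100 per arm. The same section says "Due to the nature of the study, the Program Manager will not be blind to the study arms". No blinding of participants is described anywhere in the article.

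**The concern.** In a trial that is still enrolling and assessing participants, outcome results by arm are normally kept from anyone in contact with recruitment or participants. Here the article commits to the opposite in broad terms: all findings, for the whole study period, with preliminary results named explicitly. The recipients are an advisory partner involved in recruitment materials, not an independent monitoring body.

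What is at stake is the comparison of the two arms. Suppose word spread that the tailored website does, or does not, improve literacy. That could affect who agrees to enrol. It could affect how control participants behave, since they know the tailored site will be opened to them at 6 months. It could also affect how participants in either arm rate their own confidence. Such effects could differ between arms, and the analysis could not readily separate them from the effect of the intervention.

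**Working it through.** No figure in the article bears on this point, so there is nothing to recompute. The check sets the relevant statements side by side.

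1. **What is promised.** The sentence on CSC summaries lists focus-group themes and preliminary study results as two separate items. The second item is therefore not merely another name for the first. The promise is wide in content (all findings) and in time (the whole study period).

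2. **Who receives it.** Community stakeholders, patients and health advocates, who work with the project leadership. The Recruitment section gives them a part in developing the flyers, brochures and fact sheets. It also says "we will rely on established relationships with community-based and faith-based organizations including barbershops and churches". That the members come from the same community as the participants is a reasonable inference from the committee's purpose, but the article does not state it.

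3. **Whether outcome results can exist while the trial runs.** Assessments are at baseline, 2 months and 6 months (Table 1), and the comparison of improvement is made at 2 months (Statistical analysis). Randomization is ongoing until 100 per arm, that is 200 in total. Unless all 200 are enrolled within 2 months of the first participant, some 2-month outcomes will be available before enrolment closes. Even if they were, 2-month outcomes would precede the last 6-month assessments.

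4. **Whether the outcome can be influenced.** The article uses the Sleep Apnea Literacy Scale, 24 items, to assess OSA health literacy. Participants mark how confident they are in each statement. The arms use visibly different websites, and no participant blinding is described.

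5. **Whether another section restricts the summaries.** The Data monitoring section makes data available only "once the main findings of the project have been published" and has a committee review requests. That governs data sharing with outside requesters. It does not mention the CSC, and no rule on pooling or confidentiality for the CSC summaries is given.

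Taken together, the commitment is explicit, outcome results can exist while it applies, the literacy outcome is open to influence, and nothing shown limits what is passed on.

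**The case against.** The best answer is that the sentence may mean something harmless. The project is largely developmental: building the programme is its primary objective and effectiveness is secondary. It will produce formative results from focus groups and usability testing, and the sentence names focus-group themes first. No interim comparison of the arms is described. Confidentiality rules for a committee are also the kind of detail that an article leaves to the full protocol. The first part of this stands: a reader might infer that the CSC will see results by arm, and the article does not say so. The second part does not dispose of the point, because the issue is a commitment that the article makes in plain terms, not a detail that it omits.

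Several stronger readings are tempting and are not supported:

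- **That the website could be altered mid-trial in response to results.** The article places the CSC's comments before the content is final, and has the role model stories and videos pretested before randomization. A freeze on website content is not needed on this ground.
- **That releases are unlimited in number.** The article gives no frequency.
- **That the committee has an undeclared route to changing the trial.** It has a feedback role only; nothing gives it authority over sample size, stopping or analysis.
- **That the recruitment materials would carry results.** They are described as an overview of what participation involves, and the Project Manager and Principal Investigator oversee recruitment. The concern is what committee members know, not what the flyers print.
- **That the trial is declared open-label.** That term is not used; the article states only that the Program Manager is unblinded.
- **That every outcome is self-rated.** The Apnea Knowledge Test and the S-TOFHLA test knowledge and reading comprehension and are less exposed.
- **That the listed trial status, recruiting, shows that results have been shared.** It does not.

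**Conclusion.** The point holds in a limited form. The article promises preliminary results, throughout the study, to a group that helps develop recruitment materials, and does not exclude outcome results by arm. If such results were shared before follow-up ended, enrolment, control-arm behaviour and self-rated responses could be affected.

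The size of any bias cannot be computed from the document. The conclusion rests on three assumptions: that preliminary study results could include outcomes of the randomized phase; that participants know which website they are using; and that what the committee learns can reach people being recruited or followed. If the sponsor intended only formative or pooled information, the defect is one of wording and a single sentence resolves it. The change should be made in either case, because the present text permits an exposure that is easily avoided.

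**What to change.** Amend the sentence under Community steering committee to the following effect: until the last 6-month assessment is complete and the database is locked, the CSC receives focus-group themes, usability findings and pooled recruitment and retention counts only; no outcome data by arm, and no data that could reveal the difference between arms, are released to it before then.

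This is a change of wording. It needs no change to sample size, assessments or analysis, and it leaves the committee's feedback role intact. The only cost is that the community partners wait for outcome results until follow-up has ended.
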